**Fig. 1 Fig1:**
[figure not shown]
CReSt-R Consort Diagram

### The CreSt-R intervention and control condition

#### Component 1

The CRT programme used in this study is the Computerised Interactive Remediation of Cognition-Training for Schizophrenia (CIRCuiTS). CIRCuiTS is a web-based CRT programme which targets metacognition, specifically strategy use, in addition to massed practice of cognitive functions (attention, memory, and executive functioning). Collaborative goal setting related to real-world tasks are integral to the programme with the programme tasks and exercises increasing in difficulty in response to the participant’s performance and progress. The protocol for CIRCuiTS training will follow that of a previous efficacy study [19]. This will be the primary focus of 1:1 therapy for the first weeks with remote practice sessions occurring between therapy visits. After 4 weeks, remote practice will continue and the focus of in-person therapy sessions will bridge to Social Recovery Therapy as detailed below.

#### Component 2

Social recovery therapy (SRT) focuses on addressing barriers to individuals interacting in their social environment, e.g. social anxiety. It is informed by cognitive behavioural theory and addresses individual goals. SRT follows an established protocol [20, 21]. In summary, this consists of therapy delivered in three stages. Stage 1 will include engagement and formulation with the purpose of identifying a problem list and establishing a therapeutic relationship. Stage 2 will include preparing for new activities with identification of pathways to activity and collaboration with community stakeholders. Stage 3 will include engagement in new activities using behavioural experiments to promote social activity. This is the primary focus of in-person therapy sessions from week 5 to 10 alongside remote practice of the CRT programme. There is emerging evidence to support brief intervention in both CRT [30] and CBTp [31]. Rationale for intervention duration in the CReSt-R study builds upon this recent work in addition to a previous study by our group which reported significant gains in both neuropsychological function and social function at follow-up post an 8-week, low support, remotely accessible CRT programme for chronic psychosis [32]. Intervention duration will also be considered as a feasibility indicator in this study.

In the control group of the study participants will receive treatment as usual (TAU) plus 10 weeks of 1:1 non-directive counselling matching the intervention group for time. This consists of 10 1:1, hour-long sessions with the same intervention therapist who delivers the CRT intervention. The therapy in the control condition is characterised by empathy, unconditional positive regard, congruence, and non-directivity. Notes pertaining to each session are recorded and clinical supervision is provided by the principal investigator.

The CReSt-R intervention was initially intended for delivery in in-person sessions with a strong emphasis on assertive outreach, community-embedded intervention delivery, and therapeutic rapport. However, in response to the COVID-19 pandemic and resulting public health guidelines, the protocol was revised to enable adaptation to these circumstances. The outcome measures and delivery of the intervention can now be offered face to face, entirely online, or in a blended approach remaining true to the core therapeutic principles of both components of the multicomponent intervention. These changes reflect broader change in clinical practice in response to the global pandemic and identified opportunities in this area of intervention delivery [33]. The delivery mode of the intervention will be considered in the analysis and interpretation of results.

### Feasibility

All statistical analyses will occur after completion of data collection and will adopt the intention-to-treat (ITT) principle. All data will be processed in SPSS version 27. The first objective of the analysis, assessing feasibility, will consist of descriptive statistics with derivation of means and standard deviations or medians, minimum/maximum values and interquartile range for continuous measures and proportions for ordinal or multinomial categorical and binary coded measures as appropriate. Participants’ baseline demographics and clinical characteristics will also be reported. Missing data patterns will be described for all three outcome time points.

*Process* feasibility indicators include recruitment and retention rates reported per month of trial and in total at trial completion, appropriateness of inclusion criteria and reasons for exclusion from the trial as reported by clinical collaborators, effectiveness of randomisation procedure, and effectiveness of blinding procedures.

*Intervention* feasibility indicators include participant adherence to the trial protocol, intervention duration/therapy dosage and therapy fidelity.

*Resource* feasibility indicators include therapist time in session, remote support, and clinical supervision; intervention costs for software, running costs, and participant reimbursement for assessment sessions. See Table 1 for further detail of assessment of feasibility indicators.

**Table 1 Tab1:** Feasibility indicators assessment

Feasibility indicator	Assessment
^a^Recruitment rate	% of participants recruited/time
^b^Retention rate	% of participants who complete T1, T2, and T3 outcome assessments Descriptive data on participants who leave the study early-therapy group (intervention v’s control), # of sessions completed, cited reason for leaving.
Inclusion criteria	Completion rate of referral form by clinical contact Descriptive data on reasons for exclusion from study % of participants referred to study who meet inclusion criteria
Randomisation procedure	Evaluation of 1:1 ratio at end of trial (# of intervention participants: # control participants) Logged data on any errors made
Blinding procedure	Blinding in this trial will be assessed by asking blinded assessors to guess the trial group assignment and comparing these responses to what would be expected by chance Logged data on unblinding occurrences during trial
Adherence/intervention duration/therapy dosage	# of therapy sessions completed per participant Time spent on CIRCuiTS (at-home work) per participant. (logged on CIRCuiTS software platform) Time spent on at-home behavioural experiments (logged per participant throughout trial)
Therapy fidelity	Completion rate of clinical supervision sessions Completion rate of fidelity checklists
Therapist time- in session	Total time spent by therapist in session and documentation per month (data logged throughout study)
Therapist time- remote support	Total time spent communicating via email, text, or phone outside of therapy session per month (data logged throughout study)
Clinical supervision	# of clinical supervision sessions per month
Software	Total cost of CIRCuiTs license software per month
Running costs	Total cost of study expenses per month, e.g. study phone
Participant reimbursement	Total cost of participant reimbursement for assessment sessions per month
^c^Qualitative study	Reflexive thematic analysis of semi-structured interview data
Intrinsic Motivation Inventory [34]	Completion rate and results of IMI

^a, b, c^ Key feasibility indicators for progression

Criteria for progression to a larger study will be assessed using three key feasibility indicators namely (1) recruitment rate (2) retention rate and (3) acceptability of the intervention. A system of proceed, amend, or stop will be utilised modeled on previously used traffic light systems [35] (see Table 2). This system operates on the use of guidelines rather than strict thresholds in line with current recommendations [35, 37–39]. A decision to progress the trial will be decided by the above criteria, as well as discussion with the study research team, clinical collaborators, and patient–public involvement panel.

**Table 2 Tab2:** Progression criteria

Key indicator	Proceed	Amend	Stop
**Recruitment rate** *Target figure*: 30 participants	≥ 70% of target number	51–69 % of target number	≤ 50% of target number
**Retention rate** *Target figure*: 75% of participants randomised to intervention group will complete outcome measures at T1, T2, and T3 [36]	≥ 70% of target number	51–69% of target number	≤ 50% of target number
Acceptability	Intervention is described as acceptable by participants in its current form	Intervention is described as acceptable with recommended changes to improve participant experience	Intervention is described as unacceptable by participants
Action	Continue with intervention and study design with collaboration between research team, clinical collaborators, and PPI contributors	Consultation with research team, clinical collaborators, and PPI contributors regarding necessary amendments to the intervention and study design	No progression to further trial

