### Setting and participants

This is a community-based study and will recruit participants from the Children and Adolescent Mental Health Service (CAMHS) and the Adult Mental Health Service (AMHS). Recruitment referrals from primary care providers and self-referrals are also accepted on a case-by-case basis with a primary clinical contact deemed essential for participation. Collaboration with clinical teams is anticipated to assist with recruiting adequate number of participants for this study. A sample size of 30 is a common ‘rule of thumb’ in pilot studies [26, 27], with 15 in the intervention arm and 15 in the control arm considered adequate in generating data to explore the feasibility and acceptability of the proposed intervention and in providing an estimate of the intervention’s efficacy for planning a definitive intervention trial. This pragmatic approach is consistent with other feasibility studies in the area of early psychosis [28] and in line with current recommendations for pilot studies [29].

Inclusion criteria for the study are being aged between 16 and 35 years of age, within the first 5 years of a diagnosed psychotic illness (based on time since first contact with a clinical service), community based, clinically stable and having the ability to give consent. Exclusion criteria are having a history of organic impairment (including IQ < 70), history of a head injury with loss of consciousness > 5-min duration and drug abuse in the preceding month. Confirmation of diagnosis, timeframe of onset of psychotic symptoms, presence of cognitive and social and occupational difficulties will be provided via a referral form completed by the primary clinical contact. Participants may withdraw from the study at any time.

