### Study design, randomisation, and treatment allocation

A randomised pilot study with a controlled, outcome-assessor-blind, parallel- group design will be implemented. Randomisation will use a permuted block design, using a computerised random number generator with predetermined 1:1 allocation ratio and will be completed by an independent statistician. The study research assistant will provide an information sheet to a potential participant and answer any questions they may have before obtaining written consent. There will be a 7-day cooling off period between provision of consent and enrolment to the study. Upon enrolment into the study the participants will be randomised to the intervention group (CReSt-R) or the control group. Both interventions are detailed below. After randomisation, the participant will complete baseline assessments with an assessor blind to treatment allocation. All participants will be instructed not to reveal their treatment allocation prior to each follow-up assessment. Should the blind be broken for any participant, this will be noted and reported to the principal investigator. The primary clinical contact for each individual participant will be informed of treatment allocation. The consort diagram for study procedure is contained in Fig. 1.

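### Table 2 grades retention in the CReSt-R arm only, although Table 1 defines it over all participants, so control-arm loss to follow-up cannot change the retention grade

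*Protocol article*

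**What the plan says.** The Feasibility section of the protocol article names three key indicators for progression: recruitment, retention and acceptability.

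- **Table 1** marks retention as one of these and defines it as the percentage "of participants who complete T1, T2, and T3 outcome assessments", with no restriction by arm. The same row asks for "Descriptive data on participants who leave the study early-therapy group (intervention v’s control"), with sessions completed and reasons for leaving. No threshold is attached to that description.
- **Table 2** sets the retention target as 75% of "participants randomised to intervention group will complete outcome measures" at all three time points. Proceed is "≥ 70% of target number", Amend is 51–69% of it, and Stop is 50% or less.
- **Study design, randomisation, and treatment allocation** settles what the intervention group is: participants are "randomised to the intervention group (CReSt-R) or the control group". The term does not cover both arms.

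The other two rows of Table 2, recruitment against 30 and acceptability of the intervention, do not concern control-arm follow-up. The text below Table 1 says that the system works by guidelines rather than strict thresholds, and that the decision also involves discussion with the research team, clinical collaborators and the patient–public involvement panel.

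**The concern.** One named indicator has two printed definitions, and the narrower one is graded. This is not an effect of condensing a longer protocol, since both definitions appear in the article and they differ.

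The second aim of the pilot is to find out whether the intervention can be delivered and evaluated in definitive trials, and evaluation needs outcomes from both arms. The section on estimating treatment effect sizes plans between-arm estimates at 2 and 12 weeks post-intervention from a linear mixed model, to inform power calculations for a full trial. Those estimates also depend on control follow-up. The action attached to Proceed in Table 2 is to continue with the intervention and the study design, yet no graded criterion asks whether the comparator arm of that design can be followed up. Differential loss to follow-up is a main threat to such a trial, and the retention grade cannot respond to it when the loss is in the control arm.

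**Working it through.** **Inputs.** The planned size is 30, "with 15 in the intervention arm and 15 in the control arm considered adequate" (Setting and participants), with a "predetermined 1:1 allocation ratio" (Study design). The retention target is 75%, and the bands are percentages of the target number (Table 2). The article gives no head counts for the thresholds, so there is no stated count to reproduce. The counts below assume full recruitment at 15 per arm. A completer is someone with all of T1, T2 and T3.

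**Formula.** Target = 0.75 × n. Score = completers ÷ target. Proceed if the score is at least 70%, Stop if it is at most 50%, otherwise Amend.

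**Table 2 as written (n = 15, CReSt-R only).**
- Target = 0.75 × 15 = 11.25.
- Proceed: 0.70 × 11.25 = 7.875, so 8 or more (8 ÷ 11.25 = 71.1%).
- Stop: 0.50 × 11.25 = 5.625, so 5 or fewer. Amend: 6 or 7.
- Control completers do not enter.

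**Table 1 base (n = 30, all participants).**
- Target = 0.75 × 30 = 22.5.
- Proceed: 0.70 × 22.5 = 15.75, so 16 or more.
- Stop: 0.50 × 22.5 = 11.25, so 11 or fewer. Amend: 12 to 15.

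**The same results on three bases.** The last column scores each arm against 11.25 and takes the lower grade.

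| CReSt-R / control completers | Overall | Table 2 as written | Table 1 base | Each arm, lower decides |
|---|---|---|---|---|
| 8/15, 0/15 | 8/30 = 26.7% | 71.1%, Proceed | 8/22.5 = 35.6%, Stop | Control 0%, Stop |
| 15/15, 0/15 | 15/30 = 50% | 133.3%, Proceed | 15/22.5 = 66.7%, Amend | Control 0%, Stop |
| 15/15, 1/15 | 16/30 = 53.3% | 133.3%, Proceed | 16/22.5 = 71.1%, Proceed | Control 1/11.25 = 8.9%, Stop |
| 12/15, 6/15 | 18/30 = 60% | 106.7%, Proceed | 18/22.5 = 80%, Proceed | Control 6/11.25 = 53.3%, Amend |

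The first two rows show the disagreement between the tables. The last two show that moving to the pooled base does not by itself close the gap.

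**Other reading of the bands.** If the cut-offs are taken as raw percentages of those randomised, Proceed needs 11/15 (73.3%) in CReSt-R. Then 11/15 against 0/15 (11/30 = 36.7% overall) is still graded Proceed on the Table 2 denominator. The result does not depend on how the bands are read.

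**Illustration with assumed rates.** Suppose true completion is 75% in CReSt-R and 20% in control, with independent binomial counts. The probability of a Proceed grade is P(X ≥ 8) = 0.98 on the Table 2 base, and P(X + Y ≥ 16) = 0.29 on the pooled base. With 30% in control the pooled figure is 0.54 and the Table 2 figure stays at 0.98. These rates are assumptions and do not come from the article.

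**The case against.** The strongest reply is that the gap is ungraded rather than unmonitored. Table 1 requires leavers to be described by arm, missing-data patterns are to be described at all three time points, and the decision is made by people who will have this information, using guidelines and two further indicators. That stands, and it limits the point. A reader might infer that a collapsed control arm would lead automatically to a larger trial; the article does not support that, because the retention grade is one input to a discussed decision.

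A second reply is that a target centred on the intervention arm suits the first aim, refining a novel intervention, and that Table 2 cites a source for its target which is not available here. This may explain the choice, but it does not reconcile the two tables, and it leaves the second aim without a graded check.

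Two further inferences should be resisted. One is that control participants are the more likely to leave. Nothing shows this: they receive ten hour-long individual sessions, matched for time and with the same therapist, while the CReSt-R arm also carries remote practice and at-home tasks. The other is that 12/15 against 6/15 would fall to Amend on the Table 1 base because 60% lies between 51% and 69%. The bands are percentages of the target number, so the score is 80%, which is Proceed; only a rule for each arm changes that case.

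**Conclusion.** The point holds as an inconsistency between the definition of a key indicator and the rule that grades it. As Table 2 is written, no amount of control-arm loss can change the retention grade, on either reading of the bands. With 15 per arm, 8/15 against 0/15 is Proceed under Table 2 and Stop on the Table 1 base, and 15/15 against 0/15 is Proceed and Amend respectively. The head counts rest on full and equal recruitment; the conclusion that control completers do not count rests only on the wording. It should be corrected because the pilot is meant to inform a controlled trial, but it concerns one guideline grade and not the whole progression decision.

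**What to change.** Define retention in both tables as completion of T1, T2 and T3 among all randomised participants. In Table 2, apply the existing 75% target and the existing bands to each arm separately and let the lower arm set the grade. With 15 per arm, each arm would need 8 completers for Proceed, and 5 or fewer in either arm would give Stop. State that the grade remains a guideline that feeds the discussion.

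The cost is small. Completion and early leaving are already recorded in both arms, so only the wording of the tables changes. The criterion becomes somewhat harder to pass: if true completion were 75% in both arms, the chance of a Proceed grade would go from 0.983 for one arm to 0.983 × 0.983 = 0.966 for both, assuming independence.

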### Acceptability

Acceptability of the intervention will be assessed using the Intrinsic Motivation Inventory (IMI) administered on completion of the study [34]. A qualitative semi-structured interview schedule has also been developed for completion at the end of the intervention (see Appendix 1). This embedded qualitative study will allow participants to provide feedback focusing on the following: their general experience of participating in the intervention, intervention components, experience of recruitment, communication, and perceived benefits and challenges of participating in the intervention. The qualitative data will be analysed using a reflexive thematic analysis approach [40]. The acceptability aspect of this study will be integral in further developing the multicomponent intervention and optimising clinical utility. The interview schedule itself will be reviewed for adaptation for future use based on interviewer and interviewee feedback.

### Estimating treatment effect sizes

To clarify, this study does not aim to determine treatment effect. However, to inform statistical power calculations for primary and secondary treatment outcomes in advance of a full RCT, estimates of treatment effect sizes will be obtained using linear mixed models. These analyses, completed in SPSS version 27, will provide a treatment effect estimate on each outcome measure at 2 and 12 weeks post-intervention. Outcome measures at these two time points will be entered into the model as the dependent variables with fixed effects of study arm, baseline outcome measures, time, and a time point by study arm interaction. Inclusion of baseline outcome measures accounts for their potential prediction of future outcome and will contribute towards accurate effect estimates. A random effect for participant will also be entered into the model to account for correlations between the two time points (repeated measures) per participant. This analysis will be carried out by the trial statistician.

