CRT is recognised as an effective treatment in schizophrenia generally with a large meta-analysis reporting an effect size of Cohen’s *d* = 0.45 for cognitive performance, *d* = 0.42 for psychosocial functioning and *d* = 0.18 for symptom severity [23]. CRT programmes have evolved over the years with a variety of programme protocols and specific techniques now reported in the literature. An expert working group, identified four core features of CRT, including facilitation by a therapist, cognitive exercise, procedures to develop problem-solving strategies, and procedures to facilitate transfer to real-world functioning [24]. A meta-analysis supports this emphasis, finding that better outcomes following CRT were associated with an active and trained therapist, structured development of cognitive strategies, and integration with psychosocial rehabilitation [25]. The CIRCuiTS programme, outlined in the “Methods/design” section below, embodies these core elements. It is also informed by a metacognitive model, emphasising self-awareness, self-monitoring, and self-direction when completing the programme tasks and the transfer of these skills to everyday life.

SRT is informed by cognitive behavioural theory. It is an evolved form of cognitive behavioural therapy (CBT) with an emphasis on assertive outreach and behavioural experimentation. Similar to the CIRCuiTS programme it aims to apply cognitive work and newly acquired knowledge and strategies to everyday life with a focus on self-awareness and self-monitoring.

The CReSt-R study will contribute to the cognitive remediation field and the wider field of recovery in early psychosis by exploring the feasibility, acceptability, and effectiveness of this multicomponent psychosocial intervention with the hypothesis of a greater impact on social and occupational functioning and social cognition compared to treatment as usual in the target group. Whilst both intervention components have demonstrated efficacy in previous studies in addition to being found acceptable to participants [17–22], the acceptability of the combined, multicomponent intervention to young people aged 16–35 in the early psychosis population is unknown. In addition, the feasibility of delivering the multicomponent intervention and running a larger scale randomised control trial in Ireland is unknown.

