## Methods/design

### Aims and objectives of the CReSt-R pilot randomised controlled study

The aim of the CReSt-R pilot randomised control study is to gather and analyse acceptability and feasibility data to (1) further develop and refine the novel, multicomponent CReSt-R intervention (2) investigate the feasibility of delivering and evaluating the intervention in future definitive trials. Specifically, the study objectives (outlined in further detail in “The CreSt-R intervention and control condition”, “Feasibility”, “Acceptability”, “Estimating treatment effect sizes” sections) include the following:To collect qualitative and quantitative data to assess the feasibility of the intervention with indicators in the areas of process, intervention, and resources.To investigate if the CReSt-R intervention is acceptable to young people, aged 16–35, who are within the first 5 years of a diagnosed psychotic disorder.To explore the effectiveness of the intervention by analyzing primary and secondary outcome data to provide treatment effect estimates, thus informing future trial design.

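### Fifteen per arm is called adequate for an efficacy estimate to plan the definitive trial, but that estimate is too imprecise to serve as a power input

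*Protocol article*

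**What the plan says.** Setting and participants sets the sample size by convention: "A sample size of 30 is a common ‘rule of thumb’ in pilot studies". It then makes a claim about what that number can deliver: "with 15 in the intervention arm and 15 in the control arm considered adequate in generating data" on feasibility and acceptability, and also "in providing an estimate of the intervention’s efficacy for planning a definitive intervention trial".

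Estimating treatment effect sizes opens with a disclaimer, "this study does not aim to determine treatment effect". The next sentence states the use of the estimates: "to inform statistical power calculations for primary and secondary treatment outcomes in advance of a full RCT, estimates of treatment effect sizes" will come from linear mixed models with fixed effects for arm, baseline value, time and arm by time, giving an effect on each outcome at 2 and 12 weeks after the intervention.

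The third objective gives the same purpose ("to provide treatment effect estimates, thus informing future trial design"), and the Discussion repeats it. The article names no important difference on the SOFAS, no external target and no allowance for uncertainty in the estimate. It does not limit the power inputs to SD, correlation or attrition. The only functioning effect it cites is in the Background, "0.42 for psychosocial functioning", from a meta-analysis of cognitive remediation in schizophrenia generally.

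**The concern.** Fifteen per arm can show whether recruitment, retention and delivery work. The article goes further and says that it is enough to estimate efficacy for planning the next trial. That is a stated property of the design, not a detail left to another document, and it can be checked.

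If the effect estimate is mostly noise, a sample size built on it is mostly noise too. A pilot that overestimates by chance leads to a definitive trial that is too small. One that underestimates leads to a trial far larger than needed, or to no usable sample size at all. Objective 3, informing the design of a future trial, would then not be met by the output the article relies on.

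**Working it through.** **Inputs from the article.** 15 per arm, 1:1 allocation, baseline-adjusted mixed model, d = 0.42 as an illustrative true effect.

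**Assumed, because the article gives none.** Definitive trial at two-sided 5% and 80% power. Baseline/follow-up correlation r of 0.6 to 0.7, with r = 0 as the unadjusted reference. All 30 participants analysed.

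**The plan's own figure.** 15 + 15 = 30. No formula lies behind it, so there is no calculation to reproduce.

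**Step 1: precision.** SE = sqrt((2/15)(1 − r²)) in SD units; half-width = 1.96 × SE.

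| r | SE | 95% half-width | 95% CI around 0.42 |
|---|---|---|---|
| 0 | 0.365 | 0.72 | −0.30 to 1.14 |
| 0.6 | 0.292 | 0.57 | −0.15 to 0.99 |
| 0.7 | 0.261 | 0.51 | −0.09 to 0.93 |

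These are normal approximations; using the t distribution widens them slightly (0.535 instead of 0.511 at r = 0.7). The half-width falls to 0.42 only when 1 − r² = (0.42/1.96)² × 15/2 = 0.344, that is r of about 0.81.

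**Step 2: correct sample size if d = 0.42.** n per arm = 2(1.96 + 0.842)²/0.42² = 89 (90 with the noncentral t). Adjustment multiplies both the correct and the plugged-in n by (1 − r²), so their ratio is unaffected.

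**Step 3: what a plugged-in estimate gives.** Because n is proportional to 1/d², n is within a factor of two of the correct value only if the estimate lies between 0.42/√2 = 0.297 and 0.42 × √2 = 0.594. The probability is Φ((0.594 − 0.42)/SE) − Φ((0.297 − 0.42)/SE):

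- r = 0: Φ(0.476) − Φ(−0.337) = 0.683 − 0.368 = 0.315
- r = 0.6: Φ(0.596) − Φ(−0.421) = 0.724 − 0.337 = 0.387
- r = 0.7: Φ(0.667) − Φ(−0.472) = 0.748 − 0.319 = 0.429

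So the range is about 32% to 43%. A simulation of 400,000 pilots per scenario that also estimates the SD gives 31% at r = 0 and 41% at r = 0.7. Over all its scenarios (true d 0.3 to 0.6, r 0 to 0.7, 15 or 11 analysed per arm) the figure runs from 19% to 55%. It exceeds half only in the most favourable case (r = 0.7, d = 0.6, 15 per arm).

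**Step 4: one example.** Unadjusted, an estimate one SE too high is 0.42 + 0.365 = 0.785. That leads to 27 per arm, with true power of about 33% at d = 0.42. The estimate is negative with probability Φ(−0.42/0.365) = 0.125, or 0.054 at r = 0.7.

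**Step 5: what the pilot can supply better.** With 28 degrees of freedom the 95% interval for an SD runs from 0.79 to 1.35 times the estimate. The upper 80% limit is sqrt(28/21.59) = 1.14 times the estimate, a workable allowance when planning.

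**The case against.** The strongest reply is that the article says only that the estimates will inform the power calculations. It never says that the point estimate will be the design effect or the sole input, so Step 3 describes a use the article does not commit to. That stands: the 32% to 43% is conditional on plugging the estimate in. It does not remove the point, because the article names no other input and calls 15 per arm adequate for this purpose. The widths in Step 1 do not depend on plug-in.

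A second reply is that the model adjusts for baseline, so 0.72 SD is not the precision of the planned analysis. That is correct, and the adjusted range is the relevant one. It is still wider than 0.42 unless the correlation exceeds about 0.81.

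Several stronger readings are tempting but not supported:

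- **That the article contradicts itself.** Its disclaimer about determining treatment effect can be read as declining to draw an efficacy conclusion, which is compatible with reporting estimates.
- **That a poor pilot estimate would stop the programme.** The key progression indicators are recruitment, retention and acceptability; effect size is not among them.
- **That 75% retention leaves 11 per arm for analysis.** The target covers the intervention group only and completion of all three assessments. The mixed model can use a participant with one follow-up.
- **That the interval exceeds any plausible effect.** The article gives no upper bound for the combined intervention, and 0.42 is for one component in a broader population.
- **That leaving the planning visit unnamed invites choosing the larger effect.** This is detail that a condensed article may leave to the full protocol or to the later trial.

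**Conclusion.** The point holds for the adequacy claim and for the stated use of the effect estimates. At 15 per arm the 95% half-width is about 0.51 to 0.57 SD with baseline adjustment and 0.72 SD without it, against a cited functioning effect of 0.42. The interval around that value runs from slight harm to a very large benefit. Used as the design effect, the estimate would give a sample size off by more than a factor of two in about 57% to 68% of pilots.

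The widths rest on the assumed correlations and on all 30 participants being analysed. The mis-sizing figures also rest on a true d of 0.42 and on direct plug-in; the definitive trial's two-sided 5% and 80% power are assumed too.

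This is a should-fix. The pilot's conduct, data, model and progression decision are unaffected; the harm arises only if a later protocol relies on the estimate.

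**What to change.** In Estimating treatment effect sizes, state that:

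- pilot effects will be reported with 95% confidence intervals and are descriptive only;
- the definitive trial's target difference will come from a justified important difference on the SOFAS and external evidence;
- the pilot will supply the SOFAS SD with an allowance for its uncertainty (for example the upper 80% limit, about 1.14 times the estimate at 28 degrees of freedom), the baseline/follow-up correlation, and attrition.

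In Setting and participants, remove the claim that 15 per arm suffices for an efficacy estimate for planning. Alternatively, replace it with the expected precision of the baseline-adjusted analysis over a stated range of correlations, for example half-widths of about 0.57 SD at r = 0.6 and 0.51 SD at r = 0.7 with 30 analysed. The third objective and the Discussion should be aligned.

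The cost is wording in these sections. No extra participants, data or procedures are needed. The downside is a less favourable claim for what the pilot can deliver.
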